### Randomisation and allocation concealment

The randomisation schedule was prepared by the study biostatistician (AF). All eligible participants were consecutively randomised into either the (i) real laser acupuncture; (ii) sham laser acupuncture; (iii) needle acupuncture or; (iv) no treatment group. Allocation was randomised within random permuted blocks of six to twelve generated a priori and stratified according to treating GP so that all GPs delivered approximately equal numbers in each acupuncture group to control for therapist variation. An electronic password-protected spreadsheet that contained concealed acupuncture group allocation was prepared by a researcher (BM) with no other involvement in the study, and held by an investigator (MP) not involved in recruitment, assessment or treatment. The patient code numbers for the randomised laser treatment arms were entered into the study laser machines by an independent biomedical engineer, in order to permit blinding of both the treating GPs and the participants.

### Blinding

Laser and sham laser participants were blinded to treatment allocation, as were the GPs administering laser and sham laser acupuncture, as the same machine provided both interventions and the participant code (entered by the GP) determined whether the machine actually outputted laser or not
[24]. Participants in the no treatment group are unaware that the treatment groups exist and that their data will be used for comparison (despite having consented to their longitudinal data being used for other unspecified research questions as determined by the researchers). Only the participants undergoing needle acupuncture and the GP provider were unblinded to their treatment group allocation.

### Interventions

This trial employed a combined Western and Traditional Chinese Medicine style of acupuncture, utilizing standardised acupuncture points. Such an approach reflects Australian medical acupuncture training and clinical practice. Participants were treated by experienced GPs who are also members of the Australian Medical Acupuncture College. These GPs have completed a standardised University-delivered acupuncture training course, undertaken formal accreditation by examination and a minimum period of supervised clinical experience, and are registered as medical practitioner acupuncturists by the Medical Board of Victoria. Medical acupuncturists were selected for this study to minimise potential confounder effects related to using health practitioners with varying qualifications, clinical experience and expertise. A total of 8 GPs in 9 locations around metropolitan Melbourne and regional Victoria were involved (Table 
1). The GPs had an average of 33.3 years of clinical practice and 19.6 years of medical acupuncture experience. None had less than 10 years acupuncture experience.

**Table 1 T1:** Descriptive characteristics of the general practitioners who provided acupuncture treatment

**General practitioner**	**Gender**	**Location(s)**	**Years of medical practice**	**Years of acupuncture experience**
1	Male	Bacchus Marsh	23	14
		East Melbourne		
2	Male	Anglesea	30	24
3	Male	Wendouree	48	30
4	Female	Glen Waverley	25	18
5	Male	Mildura	20	10
6	Male	Traralgon	25	12
7	Male	Malvern	50	19
8	Male	Bendigo	45	30

The GPs attended a four-hour training session run by an investigator (IR) who is an experienced medical acupuncturist, to standardise all aspects of the treatment protocol. This same investigator maintained regular contact with the GPs throughout the trial to answer any treatment-related questions and ensure compliance. Each GP was provided with a detailed treatment manual describing administration of the acupuncture interventions as well as the trial protocol. GPs were supplied with a pre-coded laser machine (custom-designed to deliver both real and sham laser) and standardized needles required for administering the acupuncture interventions.

Acupuncture treatments (approximately 20 minutes in duration) were administered once or twice weekly (at the GP’s discretion) in the GP’s rooms for 12 weeks, with a minimum of 8 and a maximum of 12 treatments delivered. Participants did not pay for treatment and the treating GPs were reimbursed for their time on a per patient basis.

The treatment protocol permitted the GPs to treat participants as they would treat patients in their normal practice. They were allowed to select from a standardized set of acupuncture points around the knee, as well as distal points on the intervention side (Table 
2). Other points could be used at the GP’s discretion depending on the cause(s) and site of the pain evident at clinical examination. These included points indicated by Traditional Chinese Medicine diagnoses in relation to Zang-Fu organ dysfunction, associated meridian and deep channel connections and ear points. Because of varying participant sensitivity, the initial treatment session permitted a maximum of six points in total, including four points on the study limb and two other points chosen as per protocol. In subsequent treatment sessions, further points were added as clinically indicated by participant response to treatment, as well as local tenderness, muscle tightness and/or swelling. Over subsequent treatments, acupuncture points were varied according to changes in participant symptoms and point reactivity. The 12-week treatment period allowed for patient attendance flexibility (a break of up to four weeks between visits was deemed acceptable for participants going away on holidays etc.), as well as for strong acupuncture responders to have several days settling time as necessary. Visits were scheduled twice per week if necessary, but weekly visits were generally recommended. Treatment was considered complete when pain and function had returned to normal, however a minimum of 8 treatments was required. Laser acupuncture interventions were administered with the patient positioned either supine or sitting over the edge of the treatment couch. Treating GPs completed standardized treatment notes after each acupuncture session. Information recorded included the acupuncture points treated and any adverse events reported by the patient from the previous session.

**Table 2 T2:** Framework of acupuncture points that could be selected by general practitioners when administering acupuncture treatments (laser and needles)

**Location**	**Acupuncture points**
Local points	SP9, 10
	ST34, 35, 36
	LR7, 8, 9
	KI10
	BL39, 40, 57
	GB34, 35, 36
	Local extra points in the hamstring muscles
Distal points	ST40
	LR3
	SP6
	GB41
	BL60
Segmental points	BL21, 22, 23
	GB30, 31
Non-segmental and general points	Ear Knee point
	DU20
	Li11
	GV14
	BL11

#### Needle acupuncture

Patients randomised to the needle acupuncture treatment underwent treatment lying down with needles inserted at the selected acupuncture points. Single-use Sierin needles (0.25x40mm) were used. The needles were inserted and left in place with the participant to rest. Needles were disposed of into a bedside sharps container at the completion of treatment.

#### Laser and placebo laser acupuncture

Laser acupuncture was administered at the selected acupuncture points using a Acupak P/L (Melbourne) laser machine that was specially manufactured for use in this trial
[24]. The laser machines were standard Class 3B laser devices that are licensed by the Australian Therapeutic Goods Association with an output of 10 mW. Energy output was 0.2 J per acupuncture point. Laser strength was checked by the manufacturer (a biomedical engineer) at study commencement, halfway through the study and will be repeated at study completion. Laser strength testing is a routine procedure in laser manufacture and maintenance and is done with a standard laser testing device. The trial laser machine had a small red non-laser light source arising from inside the probe tip that lit up when the probe was in both treatment mode and sham mode (no output). This acted as a decoy to the treatment beam, which is invisible. Therefore, neither the treating GP nor the participant could detect any difference between the real or sham laser treatment being applied. The trial laser machines were programmed by the manufacturer. At each treatment session, the GP typed the participant’s study code into the keypad of the machine, and the machine automatically delivered either laser acupuncture (ie laser output) or sham laser acupuncture (ie no laser output) according to the programmed randomisation schedule.

### Outcome measures

Table 
3 summarises the range of measures that are being collected as part of this study. The majority of outcomes are measured at baseline, 12 weeks and 12 months in all participants (irrespective of group allocation). All outcomes are collected via self-report questionnaire and mailed back to the investigators.

**Table 3 T3:** Summary of measures collected as part of the study

**Primary outcome measures**	**Data collection instrument**
Average overall pain in past week	11-point numerical rating scale (NRS)
Physical function in past 48 hours	Western Ontario McMaster Universities (WOMAC) Osteoarthritis Index 3.1 Likert version
**Secondary outcome measures**	
Average pain on i) walking and ii) standing in past week	11-point NRS
Pain over past 48 hours	WOMAC Osteoarthritis Index 3.1 Likert version
Average restriction to daily activity in past week	11-point NRS
Participant global rating of change in i) pain ii) physical function and iii) overall.	5-point ordinal scales (12 weeks and 12 months)
Health-related quality of life	Assessment of Quality of Life Instrument (AQoL II)
	12-item Short Form Health Survey (SF-12)
**Other measures**	
Psychosocial parameters	Arthritis Self-Efficacy Questionnaire
	Illness Perception Questionnaire Revised (IPQ-R)
	Medical Outcomes Study (MOS) Social Support Survey
	9-item Patient Health Questionnaire (PHQ-9)
	Revised Health Hardiness Inventory
Physical activity	Physical Activity Scale for the Elderly (PASE)
Use of health care/home assistance and work absences	Log book (retrospectively for prior 4 weeks)
Adverse events	Open-ended questioning (12 weeks)
Treatment session attendance	General practitioner treatment records (12 weeks)

All measures are recorded at baseline, 12 weeks and 12 months unless otherwise stated.

Age, gender, height, weight, duration and nature (unilateral/bilateral) of knee symptoms and previous treatment for knee joint problems were obtained by questionnaire at baseline for descriptive purposes.

#### Self-reported pain and physical function

The primary pain outcome is average overall knee pain over the past week. This is assessed using an 11-point NRS with terminal descriptors of “no pain” and “worst pain possible”. Similar scales are also being used to assess average pain on standing and on walking over the past week as secondary outcomes. Pain is also assessed, along with physical function, using the disease-specific WOMAC Osteoarthritis Index
[31]. The physical function subscale, which comprises 17 questions, is the primary outcome measure for self-reported physical function. A secondary measure of physical function is a NRS assessing average restriction to daily activities over the past week with terminal descriptors of “no restriction” and “maximum restriction possible”.

At the 12 week and 12 month assessments, participants rate their perceived change in a) pain; b) physical function and; c) overall, compared to baseline on a five-point ordinal scale (1-much worse to 5-much better). Scales of this kind are frequently used as an external criterion for comparison with changes in scores of other outcomes
[32]. Measuring participant-perceived change using a rating of change scale has been shown to be a clinically relevant and stable concept for interpreting truly meaningful improvements from the individual perspective
[33].

#### Health-related quality of life

Health-related quality of life is measured using the Assessment of Quality of Life instrument version two (AQoL II). The AQoL II has 20 questions that cover six dimensions of health-related quality of life including independent living, social relationships, physical senses, coping, pain and psychological wellbeing. The AQoL has strong psychometric properties and is more responsive than other more widely used scales
[34,35]. It produces a single utility index that ranges from −0.04 (worst possible health-related quality of life) to 1.00 (full health-related quality of life).

The 12-item Short Form Health Survey (SF-12) is also being used to measure health-related quality of life
[36]. The SF-12 is a self-administered questionnaire that was designed to measure patient outcomes in medical practice and clinical research and to evaluate the effectiveness of health interventions. The 12 questions in the SF-12 measure an individual’s perceived health across eight domains: physical functioning; role limitations because of physical health problems; bodily pain; general health perceptions; energy/fatigue; social functioning; role limitations because of emotional problems; and general mental health. The SF-12 is scored so that a high score indicates better functioning. Scoring algorithms are applied to individual item responses to produce the composite Physical Component Summary (PCS) and Mental Component Summary (MCS) scores. The PCS and MCS scores have a range of 0 to 100 and were designed to have a mean score of 50 and a standard deviation of 10; scores greater than 50 represent above average health status.

#### Psychosocial measures

A range of psychosocial measures are being collected in order to evaluate whether psychosocial parameters are associated with changes in pain, physical function and health-related quality of life observed with acupuncture.

i) Arthritis Self-Efficacy Scale is used to measure self-efficacy. It has three subscales that assess self-efficacy for control of pain management (5 questions), physical function (9 questions) and other arthritis symptoms (6 questions). Each question is rated on a 10-point NRS from 1 (“very uncertain”) to 10 (“very certain”). Prior studies have supported both the reliability and validity of this scale
[37].

ii) Illness Perception Questionnaire Revised (IPQ-R) is used to measure participant’s perceptions of their arthritis
[38]. It comprises 38 items, each rated on a 5-point Likert scale, ranging from “strongly disagree” to “strongly agree”. The IPQ-R assesses numerous dimensions including identity, timeline acute/chronic, timeline cyclical, consequences, personal control, treatment control, illness coherence, emotional representations. It has demonstrated reliability and validity
[38].

iii) Medical Outcomes Study (MOS) Social Support Survey is used to measure the perceived social support available to an individual. It comprises six questions that ask respondents to indicate how often each of six different types of support is available to them. Responses are scored on a five-point scale ranging from “all of the time” to “none of the time”. This measure of social support has been shown to have adequate validity and reliability
[39].

iv) Patient Health Questionnaire (PHQ) is a self-administered version of the PRIME-MD diagnostic instrument for common mental disorders
[40] . This trial is utilizing the PHQ-9
[41], which is the depression module that scores each of the 9 DSM-IV criteria
[42] as “0” (not at all) to “3” (nearly every day).

v) Revised Health Hardiness Inventory comprises 24 items and is used to measure health hardiness (control, commitment, and challenge) in individuals with actual health problems. Respondents indicate on a 5-point scale the degree to which they agree with the statement, ranging from “strongly disagree” to “strongly agree”. This questionnaire has adequate psychometric properties, and is a reliable and useful instrument to assess perspectives towards one’s own health
[43].

#### Physical activity levels

Habitual physical activity is measured using the Physical Activity Scale for the Elderly (PASE), a self-report questionnaire that has been shown to be reliable, valid and sensitive to change in people with knee OA
[44,45]. It records both the level and type of recreational and occupational physical activity undertaken by participants over the previous week. The PASE was developed and validated in samples of older adults (age 55+ years)
[46].

#### Use of health care, home assistance and work absences

Information on health care use (e.g. visits to hospitals, medical practitioners, other health professionals, use of investigative procedures, prescription and non-prescription drugs) and the need for paid and/or unpaid home assistance over the previous four weeks will be collected via a log-book at baseline, 12 weeks and 12 months. Participants are also asked to record any absences from paid employment (if applicable) and/or unpaid work (eg household duties, caring for family/friends) because of their health. The log-book utilises a checklist format to minimize respondent burden and to ensure high quality data is obtained with minimal data loss.

#### Adverse events

Adverse events were monitored via open-ended questioning by the acupuncturist at each treatment session and recorded in the treatment notes. In addition, participants receiving acupuncture treatment were asked at 12 weeks whether they experienced any adverse effects of treatment via open-ended questioning.

#### Treatment session attendance

Participant adherence was measured by recording the number of treatment sessions attended (out of a maximum number of 12) in the GP treatment notes.

### Sample size calculations

Our primary endpoints are average overall knee pain measured on a NRS and physical function measured via WOMAC at 12 weeks. The minimum clinically important difference to be detected in OA trials is a change in pain of 1.8 units (on NRS)
[47] and a change of 6 physical function units on the WOMAC (out of 68)
[48]. Calculations are based on an analysis of covariance (ANCOVA) adjusting for baseline of the outcome variable, and assume a between-patient standard deviation of 3.0 units for pain and 12.0 units for WOMAC
[49]. Sample size calculations for our particular study design need to take into account four aspects: clustering effects resulting from treatment of patients by the same therapist for comparisons with the control arm (hypothesis H2); dilution of the treatment effect resulting from the Zelen design
[50]; precision gain from baseline adjustment; and loss to followup. Initially assuming no clustering effects and a regular two-arm parallel RCT design with complete followup, 33 patients per arm would be required to detect the above differences in pain and function with 80% power at a two-sided 5% significance level, using ANCOVA with assumed baseline to 12 week correlations of 0.50 for pain and 0.70 for function
[49]. Adopting a conservative intra-therapist correlation of 0.10 inflates the sample size to 40 patients per arm across a total of 10 therapists. Assuming a conservative 15% non-consent rate for patients randomised to any of the three treatment arms increases the sample size by 1/(1–0.15)^2^ = 38%, and finally, allowing for 15% loss to followup, inflates the total sample size to 66 patients per arm, which we round up to 70 per arm, or 280 patients in total. Assessment of hypotheses H1 and H3 involve within-therapist comparisons only and therefore the precision loss from clustering by therapist does not apply, yielding greater power (90%) for these comparisons.

### Statistical analyses

The primary analysis of the data will be undertaken using the principle of intention-to-treat with all randomised patients included in the analyses. Demographic and clinical characteristics, as well as baseline data, will be presented to assess the baseline comparability of the intervention groups. Descriptive statistics will be presented for each group as the mean change (standard deviation, 95% confidence intervals) in the outcomes from baseline to each time point. Differences in mean change from baseline to each time point will be compared between groups using random effects linear regression modelling adjusting for baseline levels of the outcome measure and using the treating therapists as random effects to account for clustering of outcomes by therapists. Model assumptions will be checked by standard diagnostic plots. Improvement between acupuncture groups (based on the perceived ratings of change) will be compared using logistic regression with random effects as above and presented as odds ratios with 95% confidence intervals. Multiple imputation methodology will be employed to account for missing data
[51]. No statistical adjustment will be made for multiple testing. All tests will be two sided and carried out at the 5% level of significance.

As part of the secondary analyses of the primary outcomes at 12 weeks and 12 months, we plan to conduct a separate analysis to estimate the effect of treatment in the hypothetical scenario of full adherence to the randomised treatment intervention. Analytical methods for this will utilise instrumental variables methodology involving two stage least squares estimation
[52].

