**Methods/Design:**

Two hundred and eighty two people aged over 50 years with chronic knee pain have been recruited from metropolitan Melbourne and regional Victoria, Australia. Participants originally consented to participate in a longitudinal natural history study but were then covertly randomised into one of four treatment groups. One group continued as originally consented (ie natural history group) and received no acupuncture treatment. The other three were treatment groups: i) laser acupuncture, ii) sham laser or, iii) needle acupuncture. Acupuncture treatments used a combined Western and Traditional Chinese Medicine style, were delivered by general practitioners and comprised 8–12 visits over 12 weeks. Follow-up is currently ongoing. The primary outcomes are pain measured by an 11-point numeric rating scale (NRS) and self-reported physical function measured by the Western Ontario and McMaster (WOMAC) Universities Osteoarthritis Index subscale at the completion of treatment at 12 weeks. Secondary outcomes include quality of life, global rating of change scores and additional measures of pain (other NRS and WOMAC subscale) and physical function (NRS). Additional parameters include a range of psychosocial measures in order to evaluate potential relationships with acupuncture treatment outcomes. Relative cost-effectiveness will be determined from health service usage and outcome data. Follow-up assessments will also occur at 12 months.

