H8: A greater proportion of people receiving laser, sham laser and needle acupuncture will report global overall improvements compared to no treatment at 12 weeks and 12 months.

H9: A greater proportion of people receiving laser acupuncture will report global overall improvements compared to needle acupuncture at 12 weeks and 12 months.

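### The stated analysis of perceived improvement compares acupuncture groups only, so it omits the no-treatment comparator that secondary hypothesis H8 requires

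*Protocol article*

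**What the plan says.** The protocol article states two hypotheses on the global rating of change, both at the end of the Background section.

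- H8 sets each of the three acupuncture arms against the untreated arm: "A greater proportion of people receiving laser, sham laser and needle acupuncture will report global overall improvements compared to no treatment at 12 weeks", and again at 12 months.
- H9 is a contrast within the acupuncture arms: "A greater proportion of people receiving laser acupuncture will report global overall improvements compared to needle acupuncture at 12 weeks and 12 months".

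The Statistical analyses section gives one analysis for the perceived ratings of change: "Improvement between acupuncture groups (based on the perceived ratings of change) will be compared using logistic regression with random effects as above". Results are to be given as odds ratios with 95% confidence intervals.

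The sentence on the change outcomes, earlier in the same paragraph, carries no such limit: "Differences in mean change from baseline to each time point will be compared between groups using random effects linear regression modelling".

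The Abstract describes the fourth arm as follows: "One group continued as originally consented (ie natural history group) and received no acupuncture treatment".

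Table 3 lists the global rating as a five-point ordinal scale taken at 12 weeks and 12 months, not at baseline.

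**The concern.** The sentence fixes which arms enter the comparison, and that set does not match one of the two hypotheses it has to serve. A reader who follows it will fit the logistic model to the three acupuncture arms and will have no result for H8. This is not a detail that an article leaves to a fuller plan, because the article states the comparison set and states it in conflict with its own hypothesis.

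At stake is a named secondary question: whether more people feel better overall with acupuncture than without it. If the text stays as it is, the model and contrasts for H8 would have to be settled later, possibly with the data in view. The article describes follow-up as still under way, so the text can be corrected before the analysis.

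**Working it through.** No figure in the plan bears on this point. The check sets the hypotheses against the analysis text.

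**1. What the hypotheses need**

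| Hypothesis | Comparison | Times | Contrasts |
|---|---|---|---|
| H8 | laser, sham laser, needle, each vs no treatment | 12 weeks, 12 months | 3 × 2 = 6 |
| H9 | laser vs needle | 12 weeks, 12 months | 1 × 2 = 2 |
| Total | | | 8 |

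**2. What the logistic sentence supplies.** Three acupuncture arms give three pairs: laser–sham, laser–needle and sham–needle. Only laser–needle is a stated hypothesis for the global rating. Coverage is therefore 1 × 2 = 2 of 8 contrasts. The other 8 − 2 = 6 are exactly the H8 contrasts.

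**3. Whether another sentence covers H8.** The linear-model sentence compares groups without restriction, but its outcome is mean change from baseline, adjusted for the baseline value. The global rating is itself a judgement of change, has no baseline value, and enters H8 as a proportion. That model does not apply to it. The instrumental-variable analysis is limited to the primary outcomes, and the economic evaluation does not address H8. No other section gives an analysis of the global rating against no treatment.

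**4. Whether the data would exist.** The Outcome measures section says: "The majority of outcomes are measured at baseline, 12 weeks and 12 months in all participants (irrespective of group allocation"). The word for most rather than all leaves room for exceptions. However, the Procedure section has the untreated group reassessed at both times, and neither Table 3 nor the section on self-reported pain and function limits the rating to treated participants. The documents therefore point to the rating being collected in all four arms.

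**The case against.** The strongest reply is that the label is loose and no decision lies behind it. The Abstract counts the untreated arm among four treatment groups. The Randomisation and allocation concealment section calls the concealed schedule one of acupuncture allocation although it covers all four arms. The Statistical analyses section speaks of intervention groups just after saying that everyone randomised is analysed. H8 itself is explicit about its comparator, and nothing says that it is dropped. This stands in part: imprecise wording is plausible. Other passages use the labels strictly, though. The Abstract goes on to call only the other three arms treatment groups, and the randomisation section speaks of GPs delivering similar numbers in each acupuncture group, which can mean treated arms only. If all arms were intended, the sentence still says something else.

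A reader might also infer that the therapist random effects make H8 untestable, since untreated participants have no treating therapist. The documents do not support that.

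- Allocation of all eligible participants is described as stratified by treating GP.
- The same random effects serve the linear model for H2 and H4 to H6, which include comparisons with no treatment.
- The Sample size calculations section discusses therapist clustering for control-arm comparisons.

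Whatever question remains there is not specific to the global rating. For the same reason, a model in which the therapist effect acts only in the treated arms is one option among several, and this inconsistency does not require it.

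Finally, the count of 2 out of 8 measures only the literal reading. If the phrase was meant to include all arms, nothing is uncovered.

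**Conclusion.** The inconsistency is real and of low severity. On its plain wording, the stated logistic analysis serves H9 and omits the comparator for H8, and no other part of the article supplies an analysis of the global rating against no treatment. The size is 6 of 8 hypothesised contrasts on one secondary outcome. No effect on power, error rate or any estimate follows from the wording itself.

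The primary outcomes, and the other outcomes analysed as change from baseline, are compared between groups without restriction and are not affected. The article does not support reading the sentence as a decision to abandon H8; it shows only that hypothesis and analysis text disagree.

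The conclusion rests on two assumptions: that the acupuncture groups are the three arms offered real or sham acupuncture, and that the global rating is collected in the untreated arm as the article indicates. A statistical analysis plan, which is not shown, may already state the comparison correctly. The article's sentence would then still need to agree with it.

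**What to change.** In the Statistical analyses section, replace the restriction to acupuncture groups with a comparison across all four randomised groups. Name the contrasts to be reported as odds ratios with 95% confidence intervals at 12 weeks and 12 months:

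- laser, sham laser and needle acupuncture, each versus no treatment (H8);
- laser versus needle acupuncture (H9).

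State that therapist clustering is handled as in the linear model for comparisons with the control arm.

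The cost is about one sentence of text and a logistic model with one more arm. No new data, visits or participants are needed.
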